| **Statistical Considerations:** | **Primary Endpoint:**  The primary outcome (proportion of patients with PSMA-positive pathological lesions = patient based sensitivity) will be compared between tracers using an absolute risk difference (new tracer minus old tracer) with a one-sided lower 95% confidence interval for paired proportions (Wald with Bonett–Price Laplace adjustment). If the lower limit lies above -10%, we will claim non-inferiority. Detection rates per patient will be based on majority consensus reads.  **Secondary Endpoints:**   - Parametric imaging will be performed for the two radiotracers in a subset of patients (n=10*), allowing comparison of the tracers’ dosimetric and kinetic parameters, with affinity for the PSMA radioligand by calculation of the parametric equilibrium constant *K*_D,_ which will be compared between the two tracers with descriptive statistics. - The number of PSMA-positive lesions defined as pathological, benign and uncertain per region will be compared using mixed-effects Poisson regression. Patient-level data will also be analysed using the Wilcoxon signed-rank test.. - Inter-reader reliability will be compared on the region level using Krippendorff’s alpha for benign, pathological and uncertain lesions, separately for the two tracers. - Region based PPV will be calculated for each tracer separately with 95% Wilson score confidence intervals. The two tracers will be compared using McNemar’s test and an absolute risk difference with 95% confidence interval. - Semi-quantitative tumour to background ratio (defined as lesion SUV ÷ SUV of reference background region, where the background uptake is defined by convention as the left gluteal musculature) will be summarised on a region-level (i.e. using the mean over all positive lesions per region). Summarised data will be analysed using linear mixed-effects regression models. - The number and severity of adverse event will be analysed using descriptive statistics. All serious adverse events will be listed.   *The requirement for N=10 patients is justified on the previous dosimetry paper for the established PET radiotracer ^68^Ga-PSMA-11 which was adequately powered to demonstrate a mean-effective dose of 0.023 ± 0.004 mSv/MBq, i.e. with a precision in the µSv range [1]. |

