## Secondary Outcomes

- Intra-individual comparison of the parametric imaging parameter K*_D_* (measure of tracer affinity) for the two radiotracers for n=10 patients.
- The number of pathological, benign and uncertain lesions for each tracer in five regions (prostate bed, pelvic lymph nodes, extra-pelvic lymph nodes, bone, or other organs) classified by six blinded readers (three for each tracer) using previously published interpretation guidelines (PSMA-Rads 1.0)
- Inter-reader reliability between the three readers for each tracer on the level of the region with respect to three categories (pathological, benign, uncertain).
- The region-based positive predictive value (PPV), i.e. the percentage of pathological lesions that are confirmed pathological at the 6 month follow-up (based on the subset of patients and lesions with follow-up data at 6 months).
- Tumour visibility will be compared by means of uptake values (SUV) as well as tumour to background contrast in a lesion based analysis. The tumour to background ratio (TBR) is defined as lesion SUV and SUV÷ SUV of reference background region, where the background uptake is defined by convention as the left gluteal musculature.
- Number and severity of adverse events per tracer (up to 48h follow-up, see below)

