### Imaging Procedures

Imaging will be performed on the same scanner for all patients at the clinic for nuclear medicine, university hospital Bern. PET scans will be obtained using standard parameters for the scanner type. All examinations will be documented as per clinical routine. The trial physicians when reading the scans will be blinded to this report and the clinical details of the patient.

*6.1.2.1 Imaging Protocol*

Patients will receive standard PET/CT acquisitions as per institutional imaging protocol at 2h p.i. For n=10 individuals, additional dynamic imaging will be performed from the time-point of injection to 80 min (dynamic scans)

*6.1.2.2 Details of analysis*

1. A total of 6 readers will be allocated to the study. 3 readers will be allocated to read all scans for one tracer, 3 readers will be allocated to read all scans for the second tracer. This ensures that both radiotracers are interpreted separately. The odd number of readers allows for simple-majority voting in case of disagreement (i.e. where one reader rates the scan as negative and two others positive).
2. All readers will be experienced in reading scans with their respective tracer type (minimum 100 clinical scans). A training set of literature will be provided to all readers before the study commences, informing the reading physicians about potential pitfalls and normal distribution of both tracer types.
3. Visual analysis will be done according to previously published reading criteria (e.g. PSMA-RADS) to include pathological, non-pathological and diagnostically uncertain lesion types [21].
4. Reading will be done by the readers in a blinded, randomised fashion. The scans will be read at independent reading sessions. No reader will have access to the other readers’ results or interpretation.
5. Readers will report the number of lesions by lesion type (PSMA-RADS 1.0) and by region, as described above.
6. Both readers will record tracer uptake (SUV) and determine lesion to background ratio, which is defined as lesion SUV (peak) ÷ SUVmean of background reference region (defined by convention as the left gluteal musculature).
7. The principal investigator and his team will perform an unmasked scrutiny of medical records to 6-months post the second exam. Where available, a composite standard of correlative imaging, histology and prostate specific antigen will be compared affording a descriptive analysis of lesion-based diagnostic accuracy.

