## Determination of Sample Size

Power was determined using Monte Carlo simulations with 1000 repetitions and the following assumptions:

- Marginal probabilities: 80% of the patients are positive for tracer A and 80% are positive for tracer B
- Both tracers are applied to each patient
- Non-inferiority design with a one-sided alpha of 2.5%
- Non-inferiority margin of -10% (clinically acceptable margin in detection rate, balanced against the requirements for clinically realistic number of patients). We justify this margin as being less than 50% of the margin reported for superiority (22%) in a prospective trial published for ^68^Ga-PSMA-11 versus the first-generation tracer ^18^F-Choline [22].
- Non-inferiority is concluded if the lower limit of a 95% confidence interval (Wald with Bonett–Price Laplace adjustment) for the difference in the proportion of tracer-positive patients (new tracer – old tracer) is larger than the non-inferiority margin
- A pragmatic assumption is made regarding the correlation of the paired measurements. Limited data are available for this, given the dearth of comparative studies. Neither retrospective analyses [28] nor limited pilot studies [17, 27] have demonstrated any difference in detection rate. We take a worst-case scenario, and assume that both tracers are positive for 75% of the patients.

Data was simulated using function rmvbin from R package bindata [29]. With 100 patients we will have a power of 85% to detect non-inferiority.

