### Primary Analysis

The primary outcome (proportion of patients with PSMA-positive pathological lesions) will be compared between tracers using an absolute risk difference (new tracer minus old tracer) with a one-sided lower 95% confidence interval (CI) for paired proportions (Wald with Bonett–Price Laplace adjustment). If the lower limit lies above -10%, we will claim non-inferiority. Proportion of pathologic scans will be based on majority consensus reads.

The number of PSMA-positive lesions defined as pathological, benign and uncertain in each region will be analysed using separate mixed-effects Poisson regression models with tracer as fixed covariate and nested random effects for patient and region. We will report incidence rate ratios with 95% CI and p-values. As a sensitivity analysis we will compare the number over all regions using the Wilcoxon signed-rank tests and the Mann-Whitney statistic with 95% CI.

Inter-reader reliability will be analysed on the region-level based on the number of benign, pathological and uncertain lesions determined by each reader. We will calculate Krippendorff’s alpha with a ratio difference function and bootstrap 95% CI separately for each tracer.

Lesion-based PPV will be calculated for each tracer as the proportion of pathological lesions confirmed pathological during follow-up among all lesions with a known state and will be presented with 95% Wilson score CI. Using all lesions with a confirmed status during follow-up, the two tracers will be compared using McNemar’s test and an absolute risk difference with 95% confidence interval.

The semi-quantitative tumour to background ratio will be summarized on a region-level (i.e. using the mean over all positive lesions per region) and analysed using a linear mixed-effects regression model with tracer as fixed covariate and patient and region as nested random effects. The mean difference with 95% CI will be reported.

For the subset of patients with additional parametric imaging data (N=10) the planned analysis of parametric imaging parameters (see first secondary endpoint) is planned prior to completion of the study. This exploratory analysis of this secondary endpoint will not assess the primary endpoint and will not influence further trial conduct or further trial process.

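### The TBR model has no scan-level term, so its 95% CI for the tracer difference is too narrow when patients have several positive regions

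*Protocol*

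**What the plan says.** Section 6.1.2.2, item 6, defines the ratio as "lesion SUV (peak) ÷ SUVmean of background reference region (defined by convention as the left gluteal musculature"). The synopsis and section 5.2 name the same reference region. Every patient has one scan per tracer; section 11.2 lists "Both tracers are applied to each patient" among its assumptions.

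Section 11.4.2 has TBR "summarized on a region-level (i.e. using the mean over all positive lesions per region"), so the unit of analysis is patient × region × tracer. Section 5.2 counts lesions "in five regions (prostate bed, pelvic lymph nodes, extra-pelvic lymph nodes, bone, or other organs"), so a scan contributes at most five TBR values.

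The model in 11.4.2 is "analysed using a linear mixed-effects regression model with tracer as fixed covariate and patient and region as nested random effects", and "The mean difference with 95% CI will be reported". The synopsis is less specific: "Summarised data will be analysed using linear mixed-effects regression models". Neither place mentions a scan (patient-by-tracer) effect, a tracer slope that varies by patient, or a clustered variance.

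**The concern.** The regions of one scan have the same denominator. If the gluteal value of one scan is low, by measurement error or by biology, every TBR of that scan is high. Section 3.5 points to a second shared source: it allows 2 h ± 10 min for acquisition and notes that later acquisition raises tumour-to-background ratios. A true difference between patients in how the two tracers behave acts in the same way.

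The planned model has nowhere to put such variation except the residual, and it assumes residuals independent between regions. A patient with three positive regions is then counted as three independent tracer comparisons, although he supplies one pair of scans. At stake is the precision claimed for the TBR comparison, which serves the tumour-visibility objective.

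**Working it through.** **The plan's own figures.** None is given for TBR: no region counts, no SDs, no correlation, no power. The only power statement, "With 100 patients we will have a power of 85% to detect non-inferiority", concerns the primary endpoint. It reproduces: 80% − 75% = 5% discordant each way gives an exact power of 86.5% at one-sided 2.5%. It does not bear on TBR, except that 75% positive on both tracers gives 0.75 × 100 = 75 patients for a paired TBR comparison.

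**Why the intercepts cancel.** Write log TBR for patient p, region r, tracer t as

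Y = μ + β·t + a(p) + b(p,r) + s(p,t) + e(p,r,t),

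where s is what the regions of one scan share (including minus the log background) and e is specific to the region. The planned model has a, b and e but not s. The within-region tracer difference is

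d(p,r) = β + [s(p,1) − s(p,0)] + [e(p,r,1) − e(p,r,0)].

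The terms a and b are gone. Two regions of the same patient still share the s-difference, so their d values have correlation

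ρ = SD_s² / (SD_s² + SD_e²).

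**Size of the understatement.** With complete pairs the planned model estimates β by the mean of all d values, with standard error SD(d)/√(number of region pairs). The true variance is larger by

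DE = 1 + ρ·f, with f = Σm(m−1)/Σm,

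where m is the number of positive regions per patient. Non-coverage of the nominal 95% CI is 2·[1 − Φ(1.96/√DE)]. For m = 1, f = 0, so a patient with one positive region adds no inflation.

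**Assumed inputs (not in the protocol).** Log-SD of background / lesion: 0.10/0.30, 0.15/0.30, 0.25/0.25, 0.30/0.20, giving ρ = 0.10, 0.20, 0.50, 0.69. Region mixes:
- 85/15% of patients with 1/2 regions: f = 0.30/1.15 = 0.26
- 50/30/15/5% with 1/2/3/4 regions: f = 2.10/1.75 = 1.20
- all five regions positive: f = 20/5 = 4

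Worked example, second mix, ρ = 0.50: DE = 1 + 0.50 × 1.20 = 1.60; 1.96/√1.60 = 1.55; non-coverage 12.1%.

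Simulated non-coverage (75 patients, complete pairs, log scale, no true difference, 20,000 runs per setting), with the formula's value in brackets:

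| Regions per patient | ρ 0.10 | ρ 0.20 | ρ 0.50 | ρ 0.69 |
|---|---|---|---|---|
| 85/15% with 1/2 | 5.7% (5.3) | 5.6% (5.6) | 6.8% (6.5) | 7.4% (7.1) |
| 50/30/15/5% with 1/2/3/4 | 6.8% (6.4) | 7.7% (7.8) | 12.1% (12.1) | 15.2% (14.7) |
| all five | 9.9% (9.8) | 14.6% (14.4) | 26.2% (25.8) | 31.5% (31.3) |

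With no shared variation the same calculation gives 5.0–5.4%. With patient-clustered standard errors it gives 5.2–5.7% in every cell of the table.

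**Check with the full model.** REML fits of the stated model (80 patients, 15% of regions positive on one tracer only, 1,000 runs) at ρ = 0.20/0.41/0.69 gave:
- mostly one region: 6.0/7.9/11.4%
- one to three regions: 8.2/10.7/13.8%
- all five regions: 12.7/20.5/28.8%

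On the raw TBR scale at ρ = 0.41 the three mixes gave 8.4%, 9.0% and 19.2%. Adding a patient-by-tracer effect at ρ = 0.41 brought 10.7% down to 5.3% (one to three regions) and 20.5% down to 5.1% (five regions). The ratio of model SE to true SD rose from 0.83 and 0.64 to 1.00 in both.

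**The case against.** Four points can be made in the plan's defence.

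- **The inputs are assumed.** This stands. A reader might infer that a true null would be rejected up to about 2.5 times too often. The documents do not support that. A rate of 12.5% needs DE = 1.63, which means ρ = 0.63 with two regions each, about 0.32 with three, or 0.16 with five. It is neither a bound nor a central value.
- **The larger figures need background variation as large as lesion variation.** The denominator is a mean over a volume and the numerator a peak over a small region, so pure measurement noise may well be smaller below the line. Section 6.1.2.2 also has several readers per tracer and does not say how their background values are combined; averaging would shrink the measurement part. Both points favour the lower figures. Neither removes the shared part due to acquisition time or biology.
- **The text does not say intercepts only, and an unseen analysis plan may add a term.** Intercepts are the natural reading of patient and region as nested random effects. Section 11.4.2 states the structure rather than leaving it open. The synopsis sentence, taken alone, contains no error.
- **No test is planned.** This stands. Section 11.4.2 asks for p-values in the lesion-count models but only a mean difference with CI for TBR. A reader might infer that the trial would falsely declare a visibility difference, but no such decision rule exists. The supportable consequence is under-coverage.

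**Conclusion.** Wrong as written, minor severity. On the natural reading of section 11.4.2, the 95% CI for the mean TBR difference is too narrow whenever patients have more than one positive region and scan-level variation is not negligible. The mechanism follows from the protocol's own definition of TBR and its stated model. The size does not: it depends on region counts and SDs that the protocol does not give.

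Under the assumptions above, non-coverage runs from close to nominal (about 6–7%) where most patients have one positive region to about 7–15% with one to four. It goes beyond that only if many patients are positive in all five regions. One secondary interval is affected; the primary non-inferiority analysis, the sample size and the descriptive safety analysis are not.

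**What to change.** In section 11.4.2, add a random patient-by-tracer (scan) effect to the TBR model, beside the effects for patient and region within patient. Alternatively, keep the stated model and take the 95% CI from a patient-level cluster bootstrap or from patient-clustered robust standard errors. Align the synopsis sentence with whichever is chosen.

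The cost is one sentence and one model term or variance option. No new data are needed and no clinical procedure changes. The downside is a somewhat wider interval for the TBR difference.

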## Clinical Evidence to Date

This investigation for these two radiopharmaceuticals will be the first such head-to-head comparison for this patient group. By definition, no systematic reviews are available. We are aware of no evidence of any reports of adverse safety profile, history of modification or recall of either of the substances.

We note one pilot study comparing these two radiotracers by Kuten et al., albeit in in a small cohort of primary prostate cancer patients and not in recurrent prostate cancer and in a study which did not conform to standard trial methodology [17]. Likewise, a retrospective comparison by Rauscher et al [13] exists, showing no inferiority between ^68^Ga-PSMA-11 PET and ^18^F-PSMA-1007 PET, although no sample size or power estimate was included. Both studies used a two point scale (binary positive/negative) and did not consider the possibility of diagnostic uncertainty, which is an under-investigated phenomenon and which this study seeks to address. A small case series reported increased diagnostic certainty for lesions in close proximity to the bladder with additional ^18^F-PSMA-1007, although we note the lack of diuretics for ^68^Ga-PSMA-11 as major weakness of this study [15]. This will be the first clinical study of prospective, randomised design conforming to standards for evidence-based medicine. The study design incorporates reduction of bladder activity through diuretic use, in-keeping with clinical evidence and guidelines. Diagnostic certainty in these tracers has hitherto been inadequately studied.

We note that PSMA radioligand uptake can be non-specific [16], and that non-prostatic tracer uptake is reported as increased in ^18^F-PSMA-1007 compared to ^68^Ga-PSMA-11 [13]. We consider this latter point to be of high clinical relevance: unnecessary additional diagnostic testing or treatment can result from diagnostically uncertain lesions.

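### The TBR model holds region only as a nested random effect, so the reported tracer difference can be biased if the two tracers are positive in a different mix of regions

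*Protocol*

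**What the plan says.** Section 11.4.2 (Primary Analysis) first reduces TBR to one value per patient, region and tracer, "using the mean over all positive lesions per region". These values are then "analysed using a linear mixed-effects regression model with tracer as fixed covariate and patient and region as nested random effects". The reported result is a single number: "The mean difference with 95% CI will be reported".

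The regions are defined in section 5.2: lesions are recorded "in five regions (prostate bed, pelvic lymph nodes, extra-pelvic lymph nodes, bone, or other organs"). The set is the same for every patient.

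The synopsis (Statistical Considerations) says only "Summarised data will be analysed using linear mixed-effects regression models" and names no region term. The protocol nowhere adds region as a fixed effect, reports TBR by region, or restricts the comparison to regions positive on both tracers.

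**The concern.** The five regions are not a sample from a population of regions. They are fixed categories, and typical TBR can be expected to differ between, say, bone and lymph nodes. A region-within-patient intercept has expectation zero for every region, so the model gives bone and prostate bed the same mean. Systematic differences between regions are left in the variance.

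This would be harmless if each patient-region gave a value on both tracers. It does not: a region negative on one tracer gives no value for that tracer. Regions positive on both tracers supply a clean within-region comparison. Regions positive on one tracer only are compared with other regions, and so bring their typical TBR level into the tracer coefficient. The single reported mean difference can then partly describe which regions were called positive, and a reader would take it as tumour contrast.

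The lesion-count model in the same section has the same random-effects structure but is not exposed in this way, because every region has a count (possibly zero) on each tracer.

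**Working it through.** **Plan's own figure.** The protocol gives no figure for the TBR analysis. Its one computed figure concerns the primary endpoint ("With 100 patients we will have a power of 85% to detect non-inferiority"). Exact enumeration of that calculation gives 86.5%, which agrees with the stated 85% given a Monte Carlo error of √(0.85 × 0.15 / 1000) = 1.1 points. It does not bear on TBR; only n = 100 is carried over.

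**Model as written.** y = β₀ + β₁·tracer + u(patient) + v(patient, region) + e, with zero-mean random terms of variance σp², σr² and σe². The truth is set to E[y] = μ(region) on both tracers, so the true tracer effect is 0 in every region. The expected estimate is the generalised least-squares coefficient (Σ w X′V⁻¹X)⁻¹ Σ w X′V⁻¹μ, summed over all patterns of regional positivity with probability w.

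**Assumed inputs (none are in the protocol).**
- Mean TBR for prostate bed, pelvic nodes, extra-pelvic nodes, bone, other: 10, 10, 10, 5, 8.
- Positivity on the old tracer: 25, 35, 20, 12, 5%. On the new tracer: the same, except where stated.
- Positivity on both tracers in a region with rates a and b: 0.8·min(a, b) + 0.2·ab.
- Data generated with patient SD 2 and patient-by-region SD 2. The enumeration uses the variances that the nested model then fits (about 2.5 and 9.5 at residual SD 3); the region differences it cannot represent inflate the second.

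**Illustration, bone 12% versus 36%.** Positive on both: 0.8 × 0.12 + 0.2 × 0.12 × 0.36 = 10.5%. New tracer only: 36 − 10.5 = 25.5%. Old only: 12 − 10.5 = 1.5%. The crude means are 900/97 = 9.28 (old) and 1020/121 = 8.43 (new), a difference of −0.85 with no true effect. The mixed model removes part of this, because regions positive on both tracers pull the estimate towards zero.

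**Results.** Each simulation used 100 patients and 100 runs fitted by REML. Both models were fitted to the same data, so their difference cancels shared simulation noise.

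| Scenario | Expected, as written | Simulated: as written minus region-fixed | False rejection: as written / region-fixed |
| --- | --- | --- | --- |
| Bone 12→36%, residual SD 0.7 | not enumerated | −0.062 + 0.021 = −0.041 | 6% / 4% |
| Bone 12→36%, SD 1.5 | −0.16 | −0.206 + 0.043 = −0.163 | 12% / 2% |
| Bone 12→36%, SD 3 | −0.42 | −0.505 + 0.078 = −0.427 | 23% / 3% |
| Bone 12→36%, SD 5 | −0.62 | −0.743 + 0.120 = −0.623 | 20% / 5% |
| Bone 12→18%, SD 3 | −0.13 | −0.179 + 0.055 = −0.124 | 5% / 4% |
| Equal positivity, SD 3 | 0.00 | −0.066 + 0.061 = −0.005 | 6% / 4% |
| Equal region means, bone 12→36%, SD 3 | not enumerated | −0.075 + 0.077 = +0.002 | 3% / 3% |
| Prostate bed 25→50%, SD 3 | +0.08 | not simulated | not simulated |

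With region fixed, the expected value is 0.00 in every scenario in which it was enumerated. The two control rows show that the bias needs both unequal region means and an unequal mix. The last row shows that the sign depends on which region differs. Rejection rates from 100 runs are coarse (for 23%, √(0.23 × 0.77 / 100) = 4.2 points). In one further scenario, with old-tracer positives nested within new-tracer positives, the region-fixed model itself rejected in 11 of 100 runs, although its estimate was only −0.064; the model as written rejected in 22.

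**Second set of assumptions** (means: bed 10, nodes 14, bone 6, other 8; SDs: patient 3, patient-by-region 4, residual 3 to 5; 420 runs).
- Bone 15% versus 45%: bias −0.31 (residual SD 3) and −0.56 (SD 5), rejection 10.7% and 12.9%. Region fixed: 0.00 and 0.04, rejection 4.0% and 6.0%.
- Bone 15% versus 30%, residual SD 5: bias −0.30, rejection 7.1%. Region fixed: 0.03 and 5.2%.
- The standard error was the same with and without the fixed term (0.44 and 0.72).

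**Small imbalance, same means and SDs.** With bone at 15% versus 18 to 20%, the expected bias is −0.05 to −0.16 against standard errors of 0.42 to 0.73. A separate check of 15% versus 20% puts the bias at no more than about a third of one standard error.

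**The case against.** A reader might infer that the new tracer will be shown as having lower contrast, citing section 3.4, where "non-prostatic tracer uptake is reported as increased in ^18^F-PSMA-1007 compared to ^68^Ga-PSMA-11". The documents do not support that. The sentence concerns non-specific uptake and leads on to diagnostically uncertain lesions, for which the trial has separate benign and uncertain categories. It does not predict more pathological regions, and non-prostatic does not mean bone. The synopsis says that uptake is analysed for pathological lesions; the reference to positive lesions in 11.4.2 is looser, so spill-over is possible but not established. The background section (3.1) suggests better detection of local relapse near the bladder with the new tracer. That would shift the prostate bed, not bone, and could move the bias the other way. The only positivity figures in the protocol (80% per tracer, 75% on both) are at patient level, and they suggest similar and concordant findings.

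Three further objections have force.
- **Size.** Every magnitude rests on assumed TBR values, SDs and regional positivity. With a small imbalance, rejection is at the nominal level. At 15% versus 30%, 7.1% in 420 runs is barely distinguishable from 5%.
- **Reading.** The nesting order is not stated. If patient is nested within region, with a region intercept shared across patients, the expected bias in the base scenario falls to between −0.14 and −0.02 (region variance 1 to 10). That reading is less natural, but possible.
- **Remedy.** The simulations above draw positivity independently of TBR. If a region is called positive because its uptake is high, about half the bias survives a fixed region term: −0.28 against −0.57 with bone at 30%, and −0.53 against −1.13 at 45% (residual SD 3).

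None of this removes the mechanism. The protocol names the fixed and random terms, so this concerns a stated model and not a detail left to the analysis plan.

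**Conclusion.** The point holds in conditional form. On the usual reading, the TBR model cannot represent systematic differences between the five regions, and the reported mean difference can be biased if the tracers are positive in a different mix of regions. The direction is not fixed.

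Under the assumptions shown, the bias is negligible to small when the mix is nearly equal. It reaches roughly 0.3 to 1 TBR unit only when positivity in a low-TBR region doubles or triples, with the upper end arising when positivity also depends on uptake. Even a tripling does little when residual variation is small (about −0.04 at residual SD 0.7). No regional figures in the protocol allow these scenarios to be ranked.

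TBR is one of six secondary outcomes and carries no success criterion. The primary non-inferiority conclusion is unaffected. This is a low-priority improvement, worth making because it costs almost nothing.

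**What to change.** In 11.4.2, and in the matching synopsis entry, enter region as a fixed five-level factor beside tracer. Keep the patient and patient-by-region random effects, stating the nesting explicitly, and report the region-adjusted tracer difference with its 95% CI.

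Because this removes the region-mix bias but not selection of lesions by uptake within a region, add a sensitivity analysis restricted to patient-regions positive on both tracers. It drops the cells that cause the imbalance, but it still averages over whichever lesions each tracer marked, so it is a check and not a full correction.

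Cost: one model term, a few sentences and one additional fit, all on data already recorded by region. The fixed term did not increase the standard error in the calculations (0.44 and 0.72 with or without it; about 0.47 for both models in a separate check). If the region mix proves equal, nothing is lost. It should be specified before the reads are analysed.
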